#### Statistical analysis

The data obtained in this study will be entered into the Excel database by two independent persons, and the data will be analyzed by statisticians through SPSS (Statistical Product and Service Solutions) 20.0 statistical analysis software. Count data will be analyzed via the X2 test and the rank sum test for rank data. Measurements will be first tested for normality via the Shapiro–Wilk test, and measurements that conformed to a normal distribution were described via the mean plus minus standard deviation (X ± S). Comparisons between pre- and posttreatment values within groups will be made via the paired-samples t test, and comparisons before and after treatment between groups will be made using the performed via one-way analysis of variance (ANOVA). The results will be analyzed, with *p* < 0.05 as the judgment criterion for significant differences. The rank sum test will be used for nonconformity to a normal distribution.

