We reviewed the literature and reported reports of the use of Chinese medicine and acupuncture to explore the correlation between sympathetic cervical spondylosis and HRV, but no studies have analyzed the correlation between sympathetic cervical spondylosis, HRV and anxiety through Tui Na manipulation in China. We aimed to demonstrate that Tui Na manipulation can improve cardiovascular symptoms in patients with sympathetic cervical spondylosis, explore the correlation between HRV and sympathetic cervical spondylosis, alleviate anxiety, and improve the quality of life. Moreover, we hope these findings will confirm the safety and effectiveness of this therapy and facilitate its clinical promotion.

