#### Safety assessment and adverse events

During the study period, the researchers will record the adverse events at any time and assess whether they are related to the intervention. If they are related to the intervention, the intervention will be stopped immediately and recorded in the CRF form and report to the Ethics Committee of Zhejiang Hospital, and the participants will be given appropriate financial compensation. Adverse events occurring in the different treatment regimens in this study will statistically compared to evaluate the safety of the different treatment regimens. The safety evaluation is graded as follows:

Grade 1: safe, without any adverse reactions; no abnormality in the safety index examination.Grade 2: relatively safe, with mild adverse reactions, can continue the treatment without any treatment; no abnormality in the safety index examination.Grade 3: safety concerns, moderate adverse reactions, and treatment can be continued; safety indices are mildly abnormal.Grade 4: Discontinue the study due to serious adverse reactions or if there is an obvious abnormality in the safety index examination.

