#### Statistical methods

According to the prestudy observations, the best effective rate of the test group was 85%, the effective rate of the pseudomanipulative therapy control group was 40%, and the effective rate of the Western medicine group was 47%. The sample size estimation formula for the comparison of multiple sample rates was used to calculate P_max_ = 0.85, P_min_ = 0.40, *α* = 0.05, *β* = 0.10, and *ν* = 3–1 = 2, and the checking of the attached table yielded *λ* = 12.65. The number of sample cases was distributed between the groups according to a ratio of 1:1:1, and a unilateral test was used. *N* = 27 and considering a 10% shedding rate, 30 samples were needed in each group, for a total of 90 in the three groups.

$$n=\frac{2\lambda }{{\left(2\sin^{-1}\sqrt{P_{\max}}-2\sin^{-1}\sqrt{P_{\min}}\right)}^{2}}$$

$$=\frac{2\times 12.65}{{\left(\sin^{-1}\sqrt{0.85}-\sin^{-1}\sqrt{0.40}\right)}^{2}}$$

=26.6,take27

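### A between-arm significance comparison of adverse events with 30 patients per arm can describe safety but cannot confirm it

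*Protocol article*

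**What the plan says.** The section on safety assessment and adverse events states the method of evaluation: "Adverse events occurring in the different treatment regimens in this study will statistically compared to evaluate the safety of the different treatment regimens". It names no test. The same section adds an ordinal scale of four grades ("The safety evaluation is graded as follows").

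The Statistical analysis section gives one general rule for such data: "Count data will be analyzed via the X2 test", with ranked data going to the rank sum test. The decision rule is p < 0.05 "as the judgment criterion for significant differences". Adverse events are not mentioned there, but counts of events or of affected patients are count data and the four grades are rank data, so the rule covers both.

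The Background states the aspiration: "we hope these findings will confirm the safety and effectiveness of this therapy".

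The Statistical methods section derives the sample size from effective rates of 85%, 40% and 47% and concludes that "30 samples were needed in each group, for a total of 90 in the three groups". It gives no expected adverse event rate, and the article states no safety margin.

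**The concern.** Three statements combine badly. The stated means of evaluating safety is a between-arm comparison, the only criterion given is p < 0.05, and the hope is to confirm safety. A test of difference can show harm if it rejects. If it does not reject, it supports safety only when it would probably have rejected had there been a difference that matters. A trial sized for an efficacy contrast of 85% v 40% gives no such assurance for adverse events, which may be much rarer and differ by much less.

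At stake is the safety conclusion about a neck manipulation whose safety the Discussion itself describes as an open concern. The HRV outcome and the other efficacy outcomes are not affected.

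**Working it through.** **1. Where the 30 per arm comes from.** Inputs from Statistical methods: P_max = 0.85, P_min = 0.40, λ = 12.65 (α = 0.05, β = 0.10, 2 degrees of freedom).

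- n = 2λ / (2·asin√0.85 − 2·asin√0.40)² = 25.30 / 0.9768² = 26.5. The article has 26.6; both round up to 27.
- Allowing for 10% loss: 27 / 0.90 = 30.

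The figure reproduces, and only efficacy rates enter it.

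**2. Power of the adverse event comparison.** No adverse event rate is stated, so the rates below are assumptions. The test is the 3×2 Pearson chi-square, which rejects when X² > 5.991. Power is the sum, over all tables (a, b, c) that reject, of Bin(a; n, p₁)·Bin(b; n, p₂)·Bin(c; n, p₃), calculated by full enumeration.

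| True rates (test v other two arms) | n = 30 per arm | n = 27 per arm |
|---|---|---|
| 10% v 5% v 5% | 9% | 8% |
| 20% v 10% v 10% | 19% | 16% |
| 15% v 5% v 5% | 24% | 21% |
| 10% v 2% v 2% | 26% | 23% |
| 20% v 5% v 5% | 46% | 41% |
| 30% v 10% v 10% | 55% | 49% |

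A doubled rate is missed in more than four of five trials (power 9% and 19%). A tripled rate is found in 24% to 55%.

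**3. What zero events would show.** The two-sided 95% Clopper-Pearson upper limit for 0 of n is 1 − 0.025^(1/n): 11.6% for n = 30 and 12.8% for n = 27. An event with a true rate of 5% is absent from an arm of 30 with probability 0.95³⁰ = 21%; at 1% this is 0.99³⁰ = 74%.

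**4. Does chi-square hold its level?** The same enumeration with equal rates at n = 30 gives a rejection rate of 2.0%, 3.6% and 4.0% at common rates of 2%, 5% and 10%, and 4.7% and 4.9% at 15% and 20%. It does not exceed 5% at any rate checked.

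**5. Sparse tables.** The expected number of events per arm is n × pooled rate. It is below 5 when the pooled rate is below 5/30 = 16.7% (5/27 = 18.5% at 27 per arm). Example with events 3, 0 and 0 in 30, 30 and 30:

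- Expected events are 1 per arm and expected non-events 29 per arm, so X² = (4 + 1 + 1)/1 + (4 + 1 + 1)/29 = 6.21 and p = 0.045.
- Exact conditional p = 3·C(30,3)/C(90,3) = 12,180/117,480 = 0.104.

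The two fall on opposite sides of 0.05.

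**6. Would an exact test repair the power?** No. At 10% v 2% v 2% and n = 30, the exact three-group test has 19% power against 26% for chi-square. Its size is 0.3%, 1.8% and 3.6% at common rates of 2%, 5% and 10%.

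**The case against.** The strongest reply is that the article contains no rule for declaring the treatment safe. The word confirm appears as a hope in the Background, the analysis section does not mention adverse events, and the safety section names no test. A reader might infer that p > 0.05 will be reported as proven safety. No section says so, and this point does not claim it. What stands is that the article makes a statistical comparison the means of evaluating safety, gives only a significance criterion, and states an aim that this combination cannot meet.

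A second reply defends the test. A reader might infer that chi-square is invalid here because expected counts are too small. The document does not support that: it states no adverse event rate, all adverse events are to be recorded, and common mild reactions could lift expected counts above 5. The test also holds its level at every rate checked, and part of the gap in the 3/0/0 example reflects how conservative the conditional exact test is. This reply stands. The remaining caution concerns single p-values in sparse tables.

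Third, chi-square is not the only route to a safety judgement. The four grades would go to the rank sum test, and relatedness assessment and ethics committee reporting are separate safeguards. That is correct, but a non-significant rank test is no more evidence of safety than a non-significant chi-square.

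Fourth, exact tests and per-arm intervals are often left to a fuller plan that is not shown. Their absence is therefore not the complaint. The point rests on what the article states.

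**Conclusion.** The point holds in this form: the safety comparison, judged at p < 0.05 with 30 patients per arm, cannot support the hope of confirming safety. For a doubling or tripling of adverse event rates from 5% or 10%, power is about 9% to 55%. For 10% v 2% v 2% it is 26%, and an arm with no events leaves true rates of up to 11.6% open.

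The power figures rest on assumed rates, on the three-group chi-square applied to patients with at least one event, and on all 30 per arm being analysed; with 27 they are slightly lower. The 11.6% limit needs no assumed rate, only the arm size.

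The choice of chi-square is not itself an error. The issue concerns safety inference only, and it should be corrected before results are reported.

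**What to change.** In the safety and analysis sections:

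- Report, for each arm, the number and proportion of patients with adverse events, with exact (Clopper-Pearson) 95% intervals.
- Report risk differences between the test arm and each comparator with 95% intervals, and base the safety evaluation on these estimates.
- Label any p-value, from chi-square or from the rank sum test on the grades, as descriptive. An exact p-value may be added for sparse tables, with its lower power acknowledged.
- State that a non-significant difference will not be read as evidence of safety.

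In the Background, change the safety aim from confirming to describing.

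The cost is a few lines of text, with no extra patients or data. The downside is a weaker safety claim.

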### Inclusion criteria

The participants who meet the following criteria will be included in the study: (1) meetmet the diagnostic criteria of sympathetic cervical spondylosis and exclude other organs and mental diseases; (2) age between 18 and 60 years, and sex will not be limited; (3) currently in the period of sympathetic cervical spondylosis exacerbation, in addition to the main symptom of neck pain, a series of cardiovascular system symptoms such as chest tightness, panic palpitations, dizziness, and sinus rhythm or sinus tachycardia on ordinary electrocardiogram; (4) Positive in head tilt test (HUTT) or neck rotation test; (5) have a Hamilton Anxiety Scale (HAMA) score ≧7, ≦29, in line with mild to moderate anxiety; (6) have clear consciousness, pain perception and discrimination ability, and the ability to clearly describe the condition; and (7) voluntarily accept this clinical programme and sign informed consent.

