### Trial design

The main objective of this study is to observe the effect of cervical localized rotation manipulations on heart rate variability in patients with SCS. Through 24-h ambulatory electrocardiogram, changes in HRV during the treatment of sympathetic cervical spondylopathy can be observed more intuitively and objectively. To evaluate the efficacy of cervical fixed-point rotation manipulations more objectively, a pseudomanipulative therapy group will be added to the test group for the control group, and it will be observed whether there is a difference in efficacy between cervical fixed-point rotation manipulations and pseudomanipulative therapy to further clarify the efficacy of cervical fixed-point rotation manipulations.

This study is a randomized controlled trial conducted at Zhejiang Hospital to assess the effect of cervical fixed-point rotation manipulations on heart rate variability in patients with SCS. A total of 90 participants with SCS who meet the criteria will be randomly assigned to the test group (cervical fixed-point rotation manipulation group), control group (pseudomanipulative therapy group), or Western medicine group. The study has been registered on the International Traditional Medicine Clinical Trial Registry, which is accredited by the World Health Organization as a Level 1 registry, at the following URL: http://itmctr.ccebtcm.org.cn/ (the Clinical trail number: NO. ITMCTR2025000569). The protocol reporting will adhere rigorously to the SPIRIT guidelines (33). The process of the study is illustrated in Figure 1, which presents a flowchart. Furthermore, the schedule for the enrollment, treatment and assessment of the trial is show in Figure 2.

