### Outcome measures

#### Primary outcome

HRV-Related Parameters: This study will utilise a 24-h ambulatory electrocardiograph to measure three distinct groups of HRV parameters, both prior to and following treatment. The primary parameters will be evaluated encompassed the standard deviation of the mean of the R-R intervals per 5-min segment (SDANN), the standard deviation of the R-R intervals (SDNN), the proportion of neighboring R-R interval differences greater than 50 milliseconds as a percentage of the total number of heartbeats (PNN50), and the root mean square of the neighboring R-R interval differences (rMMSD).

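### The between-arm comparison is an unadjusted three-arm ANOVA with within-arm paired t tests beside it; a baseline-adjusted ANCOVA with a named test-minus-sham contrast would be a free improvement

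*Protocol article*

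**What the plan says.** The Statistical analysis section of the protocol article fixes these methods for continuous outcomes:

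- Within arms: "Comparisons between pre- and posttreatment values within groups will be made via the paired-samples t test".
- Between arms: "comparisons before and after treatment between groups will be made using the performed via one-way analysis of variance (ANOVA"). No covariate is named.
- If the Shapiro–Wilk test points to non-normality: "The rank sum test will be used for nonconformity to a normal distribution".
- p < 0.05 serves "as the judgment criterion for significant differences".

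Two other sections bear on this. Under Primary outcome, baseline HRV is available: "This study will utilise a 24-h ambulatory electrocardiograph to measure three distinct groups of HRV parameters, both prior to and following treatment". Four parameters are listed there (SDANN, SDNN, pNN50 and the root mean square of successive differences). Under Trial design, the reason for the sham arm is that "it will be observed whether there is a difference in efficacy between cervical fixed-point rotation manipulations and pseudomanipulative therapy".

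**The concern.** The stated methods fit the stated question poorly in four ways.

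1. A one-way ANOVA has no place for a baseline covariate. A baseline value of the same HRV parameter is usually the best single predictor of the post-treatment value, and the trial collects it from every patient. Leaving it out of the model costs precision that a trial of 30 per arm could use.
2. The ANOVA gives one p-value for three arms. A significant result says that the arms are not all equal; it does not say that test differs from sham.
3. The paired tests compare each arm with its own past. A significant change in one arm and a non-significant change in another is not evidence that the arms differ.
4. The Shapiro–Wilk step lets the data decide whether means or ranks are compared.

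At stake are the precision of the main comparison and the risk that readers take a pattern of within-arm p-values for a treatment effect.

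**Working it through.** **Plan's own figure.** The Statistical methods section uses "P_max_ = 0.85, P_min_ = 0.40, *α* = 0.05, *β* = 0.10" and λ = 12.65:

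n = 2 × 12.65 / (2·asin√0.85 − 2·asin√0.40)² = 26.5

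The plan prints 26.6; both round up to 27. With 10% dropout, 27 / 0.9 = 30 per arm and 90 in total. The stated size reproduces, so 27 evaluable patients per arm are used below.

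**Assumptions.** The document gives no HRV standard deviation and no baseline-to-post correlation ρ. Differences are therefore in SD units and ρ runs from 0.3 to 0.8. The SD is taken as equal before and after treatment. Tests are two-sided at 0.05; the analysis section gives only p < 0.05.

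**Precision of test versus sham.** Variance relative to ANOVA on post-treatment values:

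- post values: 1
- change scores: 2(1 − ρ)
- ANCOVA: 1 − ρ² (large-sample)

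The contrast has standard error √(2 × relative variance / 27). Power is from the noncentral t distribution with 78 degrees of freedom (77 for ANCOVA). Difference detectable with 90% power, in SD:

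| ρ | ANOVA, post values | ANOVA, change | ANCOVA |
|---|---|---|---|
| 0.3 | 0.893 | 1.057 | 0.852 |
| 0.5 | 0.893 | 0.893 | 0.774 |
| 0.6 | 0.893 | 0.799 | 0.715 |
| 0.7 | 0.893 | 0.692 | 0.638 |
| 0.8 | 0.893 | 0.565 | 0.536 |

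At a true difference of 0.6 SD (assumed), power for post values, change and ANCOVA is 59%, 59% and 71% at ρ = 0.5, and 59%, 80% and 86% at ρ = 0.7.

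**Within-arm tests.** Let test and sham have the same true change d, in SD of change. Each paired t test at n = 27 has power P, with noncentrality d√27 and 26 degrees of freedom. The arms are independent, so the chance that test is significant and sham is not is P(1 − P):

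| d | P | P(1 − P) |
|---|---|---|
| 0.3 | 0.324 | 0.219 |
| 0.4 | 0.517 | 0.250 |
| 0.5 | 0.706 | 0.208 |
| 0.6 | 0.851 | 0.127 |

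**Global test.** As an illustration, let test equal sham and let Western medicine alone be 0.8 SD lower (assumed). The noncentrality on post values is 27 × (0.267² + 0.267² + 0.533²) = 11.5. With 2 and 78 degrees of freedom the F test rejects 86% of the time, although test and sham do not differ.

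**The case against.** Several stronger readings are tempting, and the document does not support them.

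- *Baseline is ignored altogether.* The phrase on comparisons before and after treatment between groups could mean ANOVA on change, which does use baseline. The gain from ANCOVA is then smaller: 0.69 to 0.64 SD at ρ = 0.7, and 0.57 to 0.54 SD at ρ = 0.8. Against post values the gain is small near ρ = 0.3 (0.89 to 0.85 SD).
- *Test versus sham is never estimated.* The ANOVA includes the sham arm, and pairwise contrasts with confidence intervals may sit in an analysis plan that is not shown.
- *Efficacy will be concluded from the paired tests.* The section lists within-arm and between-arm comparisons side by side and does not say this. The 13% to 25% is the risk if someone reads them that way.
- *Regression to the mean will improve HRV in every arm.* Patients are enrolled "currently in the period of sympathetic cervical spondylosis exacerbation", so symptoms may well subside. The entry criteria set no HRV threshold, however, so this cannot be carried over to the primary outcome.
- *The between-arm test is invalid.* Under randomisation, unadjusted ANOVA on post values or on change is a valid comparison. Leaving baseline out of the model costs efficiency only.

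The global-test illustration also runs against the plan's own expectation: its planning rates of 85%, 40% and 47% make the test arm the outlier, not Western medicine.

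What remains is that the section does fix an unadjusted method, does not settle what the ANOVA analyses, and names within-arm tests that cannot compare arms. These are stated choices, not details left to another document.

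**Conclusion.** The point holds as a free improvement that should be made. The planned ANOVA is valid but less efficient than an available alternative, and its global p-value alone does not answer the sham question. The size of the loss depends on ρ, which the document does not give, and on which outcome the ANOVA uses. At ρ = 0.5 the detectable difference falls by 0.12 SD under either reading (0.893 − 0.774). At ρ = 0.7 it falls by 0.26 SD against post values (0.893 − 0.638) and by 0.05 SD against change scores (0.692 − 0.638). ANCOVA has the smallest variance in every case shown. The within-arm figures rest on equal assumed improvements in both arms. No size is attached to the Shapiro–Wilk step.

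**What to change.** In the Statistical analysis section:

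1. For each of the four HRV parameters, analyse the post-treatment value by ANCOVA with arm and the baseline value of that parameter. This also settles what is being compared.
2. Name test minus sham as the primary contrast and report the adjusted mean difference with a 95% CI. Make test minus Western medicine secondary.
3. Keep this model whatever the Shapiro–Wilk result. Fix any transformation in advance; for pNN50, which can be zero, it must be defined at zero (a plain logarithm is not).
4. Report within-arm changes descriptively and do not use their p-values as evidence of efficacy.

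How to handle four primary parameters together is a separate question that this change does not resolve.

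The cost is wording only: no extra patients, measurements or software, since SPSS, which the plan already names, fits this model. The change should be made before outcome data are analysed, so that neither the contrast nor the adjustment can be seen as chosen from the results.

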## Discussion

Symptoms such as palpitations and panic in SCS patients have been found to be the result of stimulation of sympathetic nerves in the posterior longitudinal ligament and intervertebral plexus (34, 35). Several studies have shown that the posterior longitudinal ligament is rich in sensory nerve fibers and is connected to the sympathetic nerves by synapses (18, 36, 37). When these sensory nerve fibers are stimulated, the excitability of the sympathetic fibers is enhanced (38, 39). The stimulation of sympathetic nerves has been demonstrated to result in the release of monoamine transmitters, such as NPY. These neurotransmitters modulate blood vessels and induce the release of substance *P* from sensory nerves, which in turn promotes the dilation of large arteries and further enhances stimulation (38, 40). As a consequence of these stimuli, the sympathetic nerves may trigger the relevant organ systems, thus engendering sympathetic symptoms, including dizziness, palpitations, and tinnitus (41). Consequently, the cervical sympathetic nerves exert a broad regulatory influence on the visceral organs (42). Given the intricacies inherent to SCS, coupled with the dearth of an unequivocal pharmacological resolution, massage therapy, an integral component of complementary and alternative medicine, is garnering heightened interest from those afflicted by SCS. This predilection stems from massage therapy’s safety profile, affordability, and accessibility, making it a viable therapeutic alternative.

Among the numerous cervical massage techniques, cervical rotational manipulation has garnered favorable feedback in the management of cervical spondylosis (20). As Moser et al. reported, cervical rotation manipulation has been demonstrated to reduce reverse blood flow and velocity within the vertebral artery (43). Guan et al. conducted a series of experiments on animals to ascertain the safety of cervical rotation manipulation (44). The results of these experiments demonstrated that this manipulation technique does not result in damage to blood cells, thus confirming its safety (44). With the application of biological finite element technology in the field of biomechanics, several scholars have found through computational modeling that cervical rotation manipulation changes the stress distribution around the cervical spine and improves the biomechanical equilibrium around the cervical spine (21).

Compared to other traditional cervical spine manipulation techniques, the cervical fixed-point rotation manipulation is highly targeted during operation, with a key feature being its “accuracy.” First, precise localization is essential. During this technique, the practitioner first performs a palpation to determine whether the pathological site is in the muscles (muscle bands) or the cervical spine (joint dislocation), and then confirms the dislocated joint based on imaging diagnostics. Secondly, the timing of the manipulation is precise. During the procedure, the cervical spine should be rotated to its maximum extent or moved to the “trigger point” where resistance is felt, at which point a controlled, slightly increased-amplitude, instantaneous manipulation is performed. Compared to traditional cervical rotation manipulation techniques, the cervical fixed-point rotation manipulation technique is more targeted and precise in addressing the affected cervical segments and muscles, has the effect of correcting joint dislocation, realigning anatomical structures, and relieving muscle spasms, resulting in clearer effects. Clinically, it is primarily used for cervical spondylosis with nerve compression, such as radicular cervical spondylosis and sympathetic cervical spondylosis.

Previous studies of cervical rotational manipulation did not explore the patient’s cervical spine lesion nodes for treatment and consider other systemic diseases, did not truly improve the patient’s symptoms, and mostly assessed the efficacy in the form of questionnaires, which lacked objective and scientific evaluation standards; however, HRV has the advantages of being accurate, noninvasive, simple to operate, and dynamically observable and can be used as an objective standard for evaluating the efficacy of treating patients with SCS. This study is the first to analyze the correlation between heart rate variability and the SCS by means of Tui Na manipulation and to propose an objective and reliable evaluation index.

Despite the proven effectiveness of cervical rotational manipulation in the treatment of cervical spondylosis, its safety remains a concern. Many people are concerned that improper manipulation may cause more damage to the blood vessels and nerves in the neck. Because of the requirements for the angle and strength of the manipulation, more clinical protocols are needed to ensure the safety of the manipulation and to better serve the clinic. In this study, for the first time, the cervical spine was adjusted segmentally and locally through cervical fixed-point rotational manipulation, which was more targeted to the cervical spine of the diseased segments, and manipulative operations and strengths were described during the study to ensure that the manipulative operations were carried out within the safety limits.

However, there are still limitations in this study. Although HRV can be used as an objective criterion for assessing the efficacy of SCS patients, there are episodes and flattening of symptoms in SCS patients, and the assessment is more accurate only when the patient is in the episodic phase with symptoms such as panic attacks and palpitations, so there is a limitation on the time point of assessment. In addition, there are few clinical reports on the correlation between SCS symptoms and HRV, and the reliability of HRV assessment is controversial. Therefore, more attention should be given to the validity and reliability of the HRV in the assessment of efficacy in SCS patients in future clinical studies. Greater emphasis must be placed on the necessity of standardizing and assessing the safety of cervical rotation manipulation. In the future, the employment of biological finite element analysis will facilitate the calculation of more precise manipulation angles and force parameters; this, in turn, should result in a more effective promotion of the cervical method of manipulation, leading to substantial improvements in the quality of life of SCS patients and, by extension, the overall health of the population.

